### Executive functions

Executive functions (EFs) collectively refer to a set of cognitive skills [34, 35] including inhibitory control, planning and cognitive flexibility. Emotion regulation (ER) is an integral part of self-regulation, which is a complex concept that regulates emotions, motivation, cognition (e.g., attention), social interactions, and physical behavior [36].

Our measurements are designed to capture the emergence of executive function at 1 year ± 1m, 2-years ± 2m, and 3-year ± 2m of age. The tests for these age groups are:

For cognitive flexibility and working memory: Spin-the-Pots, Knock and Tap tasksFor inhibitory control: Glitter Wand task

### Electroencephalogram (EEG)

The EEG reflects the summation of large populations of neurons that propagate to the scalp surface. These currents can be measured by placing sensors on the scalp [37]. The EEG will be recorded using a NetAmps 300 amplifier system, a 128-channel HydroCel Geodesic Sensor Net (HCGSN, Electrical Geodesics Inc., Eugene, OR) and data acquisition software (NetStation 4.5, EGI). EEG will be used to investigate functional connectivity, power spectrum and event related potentials (ERPs) in both resting-state and during execution of different cognitive tasks.

### Eye tracking

Eye tracking will be used to test distractibility, or disengagement. Children will be presented with an interesting visual stimulus (adapted from Elsabbagh et al) [38] and will be tested on how they disengage their attention from that stimulus. This test has been validated in other low-income settings [39].

A TOBII eye-tracking system (Tobii Studio version 3.3.0) will be used to track participant’s eye movements during cognitive tasks. A small infrared camera (Logitech QuickCam Pro 9000 Webcam V-UBM46 USB Camera Mic Carl Zeiss 2MP) mounted to a computer monitor will track eye movements.

### Functional near infrared spectroscopy (fNIRS)

fNIRS, a non-invasive method suitable for infant studies [40], will be used to measure brain activity that is related to an externally presented stimulus, and to measure activity connections between different parts of the brain with no explicit external stimulus presentation.

fNIRS will be performed using the NTS system (Biomedical Optics Research Laboratory, University College London). This system meets the international standards: IEC 60601 (for medical electrical equipment), and IEC 60825 (for safety of laser products). This system has been used to image brain activity in over 300 healthy infants in London, and 100 infants in Gambia [41].

### Language environment analyses (LENA)

The frequency of vocalization or verbalizations and conversational turns in children will be measured. Recording data at multiple time points will provide a measure of the consistency of the language environment. Data will be analyzed using LENA analysis software (LENA Online Version 3.0). The algorithm will determine the number of child and adult vocalizations, conversational turns, and other language measures [42–44].

### Parent child interaction (PCI)

A 10-15minute interaction between parent and child will be video recorded and transcribed. Parents will be asked to engage their child in play or in conversations in the presence and absence of toys and books. The child will also play with the toys/books while the parent completes short surveys, or watches a short video. Language transcripts and videos will be coded for the child’s and parent’s use of language and mutual engagement.

### Bayley scales of infant and toddler development, fourth edition (Bayley 4)

Bayley 4 is an extensive formal developmental assessment tool for diagnosing developmental delays in early childhood. Bayley 4 assesses development in children of 1–42 months of age in 5 domains: cognition, motor, language, socio-emotional, and adaptive behavior and plays a potential role in assessing EF in infants [45].

### Behavioral assessment questionnaires

SDQ (Strength and Difficulties Questionnaire), PSS (Perceived Stress Scale), FCI (Family Care Indicator), HOME (Home Observation Measurement of the Environment), BRIEF-P (Behavior Rating Inventory of Executive Function—Preschool Version), BISQ (Brief Infant Sleep Questionnaire)–Revised Short Wolke’s behavioral rating and COVID questionnaire and CPAS (childhood psychological adversity questionnaire) will be administered for behavioral assessments of both mother and child at different time points in the study (Supplementary materials). These questionnaires have previously been validated and used in the Bangladeshi population [46–49].

### Biological samples

Biological samples (blood, stool and buccal swabs) will be collected, prepared and preserved following standard operating procedures (SOPs) created for this protocol (S2 File).

### Blood analytes

Child’s peripheral blood (2–3 ml) will be collected (EDTA vacutainer), separated into plasma and red blood cells and immediately frozen (-80°C), to enable measurement of vitamin and mineral micronutrients, functional lipids, and microbiome derived blood metabolites (Sample code “33”). Peripheral blood samples will be collected from the control and intervention arms: at enrollment 1year ± 1m, 2years ± 2m, and 3 years ± 2m. In the intervention group, an additional sample will be collected during anthropometric recovery or following the 3-month E-RUSF/ RUSF intervention. Peripheral blood samples will be collected from the outcome reference arm group only at enrollment. Samples will be used for low pass whole genome sequencing (Gencove) and discovery metabolomics.

### Stool collection

Child fecal samples will be collected (Zymo Fecal collection tube, OMNImet. GUT ME-200 tube according to the manufacturer’s instructions, sample code “10”). Samples will be used for shotgun metagenomic (20M 250bp reads per sample) sequencing, functional pathway analysis and stool metabolomics. Fecal samples will be collected from the control and intervention arms at enrollment (1year ± 1m, 2years ± 2m, and 3 years ± 2m). Additional samples will be collected during anthropometric recovery for the intervention group and following the 3-month E-RUSF/ RUSF intervention. Stool samples will be collected from the outcome reference arm only at enrollment.

### Buccal swab

Buccal swabs will be collected using mini-swabs (MS-01) and BuccalFix tubes BFX/S1/05/50 (Isohelix, according to the manufacturer’s instructions). Samples will be coded as “20” for genomic/epigenomic studies. Buccal swabs will be collected from the control and intervention arms at enrollment 1year ± 1m, 2years ± 2m, and 3 years ± 2m. Buccal swab samples will be collected from the outcome reference children only at enrollment.

### Maternal assessments

Weight and heightOne stool sample (5gm non diarrheal stool sample)One buccal swab sample5 ml peripheral blood collected in an EDTA tube

These samples will be collected from the mother during the baseline assessments of all enrolled children. SOPs and CRFs for the collection of these maternal biological samples are supplied (Supplementary materials).

### Study risks and confidentiality

Participant confidentiality is rigorously maintained by the involved investigators, their team, the sponsor and their representatives. This confidentiality encompasses records, research data, clinical details of participants and all other data generated during their involvement in the study. Each participant will be assigned a unique study identification number (SID) for use on study documents and in the study database to minimize risks to confidentiality. The document connecting the SID to patients’ names and medical records will be securely stored in a locked office and will not be accessible to individuals not affiliated with the study. All computers containing the study database will be password-protected ensuring that only authorized personnel associated with the study can access the database.

All neuroimaging/behavioral procedures in this study, have been performed in various studies worldwide, are non-invasive, pain free, and are not known to induce adverse effects in participants. Devices have been adapted to the infant population to ensure safety and comfort, and every measure proposed for use in this project is currently being used in the Crypto and PROVIDE Cohorts in Mirpur. Children will be constantly monitored, and the experimenter will pause the session if children become fussy or fidgety. If children become difficult to be placated, the sensors will be removed to end the session.

To minimize the risk of fatigue from the neuroimaging testing, we have split the battery of tests into two sessions, with options for breaks and snacks as required.

### Data monitoring and quality control

A quality control team, comprised of investigators, field research officers and other team members with experience in field activities, will be responsible for regular observations at the study site and checking data for validity and completeness. For 3–5% of study participants, the quality control team will independently repeat data collection, on the same day, using a field-tested format. Errors will be addressed and corrective measures will be undertaken immediately. All data collection forms will be checked, within the evening they were collected, for completeness, accuracy and consistency. Identical forms, definitions and methods will be used throughout the study period. Weekly staff meetings will be held to review the progress of the study.

Behavioral and early learning data will be collected on a selected subset (5% of children) in parallel, by the quality check (Q/C) officer. The Q/C officer will also undertake qualitative scoring and quality check tests on tester performance, using a semi-structured check-list (Supplementary materials). All test information will be reported.

### Adverse events (AE) and serious adverse events (SAE)

All AEs and SAEs, related or unrelated to the study feeds, will be reported for this protocol. AE and SAEs will be assessed for severity, relationship to the study intervention, actions taken and outcomes. All SAEs will be reported to the Ethical Review Committee of icddr,b, within 24 hours of the study staff becoming aware of the event. All participants will be provided free primary care for any AEs reported at the study clinic.

### Data analysis plan

The study will result in a rich data set consisting of neuropsychological assessments of executive functions and emotion regulation, blood nutriome and metabolome, microbiomes, genetics, nutritional status, age, sex, DOB, demography and SES from family, medical history of these children.

Statistical tests will be conducted to quantify differences in the neurocognitive assessments (e.g. EF, NIRS and EEG responses) between and within the wasted and non-malnourished cohorts, all of whom have varied levels of exposure to adversities (single adversities, composite exposure scores, and income). Three model types will be employed, (a) a t-test for analyzing univariate outcomes, (b) linear mixed models, and (c) structural equation modeling to analyze multivariate outcomes.

T-tests will be conducted with an alpha level of 5% and the distributions of the two samples will be checked for normality, homogeneity of variances and autocorrelation in the residual terms. The False Discovery Rate (FDR) method will be applied to correct for potential multiple comparisons.

Linear mixed effects model will be used to evaluate longitudinal effects with respect to the group differences and the relationship with other earlier biological and/or psychosocial risk factors, particularly focusing on the brain power and functional change in development. Since these measurements are repeated at three time points, mixed models with either random intercept or random slope will be considered.

Structural equation modeling will be used to evaluate multivariate relationships. Model fit will be evaluated using descriptive fit indices such as the Comparative Fit Index (CFI) which work with relatively small sample sizes (Bentler et al, 1990) [50].

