### Sample size

Power for comparisons between well-nourished (WLZ/WHZ > -1 SD) and wasted children (-3≤ WLZ/WHZ <-2 z-score, and/or 11.5≤ MUAC <12.5 cm) at 1 and 3 years was estimated using the Student’s t-test and Structural Equation Modeling (SEM). For the t-test, the proposed medium level difference between the two groups (i.e. 2 standard deviation) requires a minimum of 51 participants per group for power equal to 80% using a level of significance equal to 5% (for a one-tailed test).

Sideridis et al. 2014 [23] used a series of Monte Carlo simulations to estimate that 50–70 participants would suffice to evaluate functional connectivity in the brain using EF, EEG or fMRI. Sideridis et al.’s simulation involved medium sized models (i.e. 7 latent variables), but the model size is inversely related with sample size. Therefore, larger models, like those in the present study, require fewer participants.

To account for participant drop out during the follow-up period, sample sizes were increased to n = 70 children in each group.

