### Assessments

Assessments (neuropsychological, behavioral, nutriome, metabolome, and microbiome) will be conducted at baseline, during anthropometric catchup, at 2 and 3 years.

Age, sex, date-of-birth, demography and socio-economic status, medical history, and feeding history will be collected at the time of enrollment.

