### Neuropsychological assessment

Neurodevelopmental assessment data for the control and intervention groups will be collected at enrollment (1year ± 1m), 2years ± 2m, and at 3 years ± 2m. Neurodevelopmental assessment data for the outcome reference group will be collected only at enrollment.

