## Discussion

### Strengths and limitations of this study

This study aims to assess the impact of nutritional and psychosocial interventions on the cognitive and emotional well-being of malnourished children in a low-income setting. We are piloting a nutritional intervention to improve brain health and we will use tools that directly measure EF and ER as well as their response to interventions. The study’s findings may be constrained due to the potential influence of psychosocial adversities, unhygienic living conditions, suboptimal sanitation practices, with accompanying infection, and worm infestation as malnutrition often co-exists with these factors.

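### The wasted versus well-nourished contrast is not randomised, yet it is powered by, and listed for, a t-test that cannot use the SES and adversity data the trial collects

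*Protocol article*

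**What the plan says.** The Allocation section of the protocol article randomises only the one-year-old MAM children, 1:1 to Group A or Group B. The well-nourished controls and the three-year-old MAM reference group are recruited separately, by nutritional status and age (Recruitment, Table 1; Control groups).

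The Sample size section opens with "Power for comparisons between well-nourished (WLZ/WHZ > -1 SD) and wasted children" at 1 and 3 years, and uses Student's t-test (with SEM alongside). The Data analysis plan directs its tests at differences "between and within the wasted and non-malnourished cohorts" and continues: "Three model types will be employed, (a) a t-test for analyzing univariate outcomes", followed by linear mixed models and SEM. The checks attached to the t-test are normality, equal variances, autocorrelation and an FDR correction. No covariate is attached to it.

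The same section describes the cohorts as "all of whom have varied levels of exposure to adversities (single adversities, composite exposure scores, and income". The Assessments section states: "Age, sex, date-of-birth, demography and socio-economic status, medical history, and feeding history will be collected at the time of enrollment". The limitations paragraph adds that the "findings may be constrained due to the potential influence of psychosocial adversities, unhygienic living conditions" and related exposures.

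**The concern.** Nutritional status in this population travels with income, home environment and adversity, and these plausibly affect executive function and emotion regulation whatever the child's nutrition. A two-sample t-test on groups formed by nutritional status compares all of that at once. The plan recognises the imbalance and collects the variables, but the method it lists for univariate outcomes cannot use them. The safeguards it lists address distribution and multiplicity. FDR control limits the share of false discoveries when the null distributions are right; it does not correct a difference whose null value has moved away from zero.

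At stake is the powered contrast. If poorer families are over-represented among wasted children and lower SES goes with lower scores, the bias points the same way as the expected result, so a reader would have no warning from its sign.

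**Working it through.** **The plan's own figure.** The Sample size section gives 51 per group for 80% power, one-sided 5%, with "the proposed medium level difference between the two groups (i.e. 2 standard deviation". With n per group = 2(z₀.₉₅ + z₀.₈₀)²/d² = 2(1.645 + 0.842)²/d²:

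- d = 2: 3.1, so 4 per group (exact t also gives 4, power 0.80).
- d = 0.5: 49.5, so 50 per group; exact t gives 51, power 0.806.

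The stated 51 therefore follows from 0.5 SD, not 2 SD. That is a separate point, but it makes 0.5 SD the yardstick here and confirms that the design rests on an unadjusted two-sample t-test.

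**Bias of the unadjusted difference.** The documents give neither the SES gap between groups nor the strength of the SES–outcome relation. Both are assumptions:

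- gap dx = 0.3 to 0.7 SD;
- slope r = 0.2 to 0.4 outcome SD per SD of SES.

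Bias = r × dx:

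- low: 0.2 × 0.3 = 0.06 SD (12% of 0.5 SD);
- middle: 0.3 × 0.5 = 0.15 SD (30%);
- high: 0.4 × 0.7 = 0.28 SD (56%).

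**Rejection rate with no true difference.** Noncentral t, with noncentrality = bias / √(1/n₁ + 1/n₂). The standard error is 0.198 at 51 v 51 and 0.169 at 70 v 70. For the middle case at 70 v 70 the noncentrality is 0.15/0.169 = 0.89.

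| Bias (SD) | 51 v 51, two-sided 5% | 70 v 70, two-sided 5% | 70 v 70, one-sided 5% |
|---|---|---|---|
| 0.06 | 6% | 6% | 10% |
| 0.15 | 12% | 14% | 22% |
| 0.28 | 29% | 38% | 50% |

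The analysis section does not state sidedness. The sample size is one-sided; that column assumes the bias runs in the tested direction.

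**Price of adjusting.** For equal groups and one covariate, the variance factor is (1 − r²)(1 + dx²/4). The first term is the gain in precision, the second the cost of the imbalance.

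- Middle: 0.91 × 1.0625 = 0.97, so 51 becomes 50.
- Most favourable (r = 0.4, dx = 0.3): 0.84 × 1.0225 = 0.86, so 44.
- Least favourable (r = 0.2, dx = 0.7): 0.96 × 1.1225 = 1.08, so 55.

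All stay below 70 per group.

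**Does the mixed model already cover this?** The Data analysis plan gives it to longitudinal effects over three time points, examining group differences and the relationship with earlier biological or psychosocial risk factors. It does not say that those factors adjust the group contrast, or that the model takes precedence over the t-test at a single age. SEM is assigned to multivariate outcomes. Read as written, a univariate comparison at age 1 or age 3 goes to the t-test.

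**The case against.** The strongest reply is that the t-test is one of three model types. The wasted and well-nourished children are both measured three times, so a mixed model with psychosocial factors could estimate their difference at every age. On that view only the choice of lead model and the covariate list remain open, and both commonly sit in an SAP. This stands in part: a reader might infer that the plan is unadjusted throughout, and it is not. What remains is that the article positively assigns a method unable to adjust to univariate outcomes and sizes the study on it. That is a stated choice, not an omitted list.

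Three other inferences go too far.

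- *That treated children will be compared with the three-year-old reference group by t-test.* The analysis section assigns no test to that group. It is true that "Neurodevelopmental assessment data for the outcome reference group will be collected only at enrollment", so it fits poorly in a three-time-point model, but reaching the t-test by elimination is not stated text, and SEM is also listed.
- *That confounding will be reported as an effect of malnutrition or treatment.* No section says so. The tests are meant to quantify differences, and the limitations paragraph acknowledges adversity.
- *That the false-positive rate nears one half.* A pooled two-sided test of 140 v 70 gives 48% at 0.28 SD, but the plan does not state that test. It would merge arms on different feeds after baseline and ignores dropout.

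The sizes also rest on assumed inputs. All groups come from the same Mirpur wards, described as typical urban poor, which may narrow the SES gap and make the upper end unlikely.

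**Conclusion.** The point holds for cross-sectional comparisons of wasted with well-nourished children. That contrast is observational, the plan powers it with a t-test and lists a t-test for univariate outcomes, and nothing stated gives the adjusted model precedence. The excess in false positives runs from negligible to severe, depending on an SES gap and slope that the documents do not supply, and on the linear relation assumed here. Adjustment removes the bias only for covariates that are measured and correctly modelled. For the three-year-old reference group the conclusion is conditional: no test is fixed, and if one is run, adjustment cannot repair the difference between children selected with MAM at 1 year and children found with it at 3. The randomised comparison of Group A with Group B is not affected.

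**What to change.** - For every cross-sectional contrast with the well-nourished group, name as main analysis a linear model with group, SES/income, the adversity composite, sex and exact age at testing. Age belongs there because the testing windows run from 11 to 13, 22 to 26 and 34 to 38 months. Where a covariate is measured repeatedly, use the enrolment value, since home measures may respond to the stimulation programme.
- Keep the t-test as a descriptive, unadjusted companion and label the contrast an association.
- State how the longitudinal mixed model relates to these analyses, and whether its psychosocial terms are adjustment covariates.
- If treated children are compared with the three-year-old MAM reference group, use the same adjusted model, call the result an association and state the selection difference. This matters for the stimulation aim: both randomised arms receive stimulation, so Group A versus Group B cannot estimate its effect.
- Limit causal treatment claims to Group A versus Group B.

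The cost is a wording change and a few degrees of freedom. SES, income, adversity, sex and age are already in the planned data set, so no new data collection is needed.

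### For Group A versus B, the stated t-test gives up the precision in the enrolment score, and the random-intercept option can misstate the standard error of change

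*Protocol article*

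**What the plan says.** The Data analysis plan lists three model types: "a t-test for analyzing univariate outcomes", linear mixed models, and structural equation models. No covariate or baseline term is attached to the t-test. On the mixed model it says: "Linear mixed effects model will be used to evaluate longitudinal effects with respect to the group differences". It adds the relation with earlier biological or psychosocial risk factors, and then, giving the three measurement times as the reason, that "mixed models with either random intercept or random slope will be considered".

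The Neuropsychological assessment section gives the visit schedule: "Neurodevelopmental assessment data for the control and intervention groups will be collected at enrollment (1year ± 1m), 2years ± 2m, and at 3 years ± 2m". The Executive functions section covers the same three ages: "Our measurements are designed to capture the emergence of executive function at 1 year ± 1m, 2-years ± 2m, and 3-year ± 2m of age". Every randomised child is therefore due a pre-treatment score. The outcome reference group is assessed once only.

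The Sample size section bases its t-test calculation on 51 per group, one-tailed 5%, 80% power, raised to 70 for dropout.

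**The concern.** Two stated choices could be improved for the randomised comparison.

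First, a t-test on the 2- or 3-year score makes no use of the child's enrolment score. Randomisation keeps the comparison unbiased, but variance that the baseline could explain stays in the error term. If dropout leaves only 51 per arm, there is little power to spare.

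Second, a random intercept alone forces one common correlation on all pairs of visits. Scores two years apart in very young children may well correlate less than scores one year apart. The model then averages the correlations. Its standard error is too small for the most distant pair and too large for a closer, more highly correlated pair. The section says that it focuses on developmental change, and the 1-to-3-year contrast is the affected quantity.

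**Working it through.** **Inputs.** From the Sample size section: 51 per group, one-tailed 5%, 80% power. From the Neuropsychological assessment section: visits at 1, 2 and 3 years. The document gives no between-visit correlations, so they are assumed below and shown over a range.

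**Reproducing the plan's figure.** With a difference of 0.5 SD, one-sided 5% and 80% power, the noncentral t calculation gives 50.15, rounded up to 51. So 0.5 SD is the effect used here. The 2 SD printed in that section would need only 4 per group; that is a separate matter.

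**Step 1: precision from the baseline.** Let r be the 1-to-3-year correlation. Relative to a t-test on the 3-year score, baseline adjustment multiplies the variance by 1 − r². The equivalent sample size is 51/(1 − r²).

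| r | 1 − r² | Equivalent n per arm | Power, one-sided 5% | Power, two-sided 5% |
|---|---|---|---|---|
| t-test | 1.00 | 51 | 81% | 71% |
| 0.2 | 0.96 | 51/0.96 = 53 | 82% | 72% |
| 0.3 | 0.91 | 51/0.91 = 56 | 84% | 75% |
| 0.5 | 0.75 | 51/0.75 = 68 | 89% | 82% |

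**Step 2: random intercept alone.** Assume complete data, equal variances at the three visits, and correlations r12, r23, r13. The random-intercept model estimates one common correlation, the mean m = (r12 + r23 + r13)/3. For the group difference in change between visits j and k, the true variance is proportional to 1 − rjk and the model's to 1 − m. So

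model SE / true SE = √[(1 − m)/(1 − rjk)].

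Type I error at nominal two-sided 5% is 2·[1 − Φ(1.96 × ratio)].

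| r12, r23, r13 | m | 1-to-3-year ratio | Type I error, 1-to-3 | 2-to-3-year ratio | 1-to-2-year ratio |
|---|---|---|---|---|---|
| 0.4, 0.6, 0.3 | 0.433 | √(0.567/0.7) = 0.90 | 7.8% | √(0.567/0.4) = 1.19 | 0.97 |
| 0.5, 0.6, 0.3 | 0.467 | √(0.533/0.7) = 0.87 | 8.7% | √(0.533/0.4) = 1.15 | 1.03 |
| 0.3, 0.5, 0.2 | 0.333 | √(0.667/0.8) = 0.91 | 7.4% | √(0.667/0.5) = 1.15 | 0.98 |

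Simulation with 51 per arm and 20,000 replicates gave 7.7%, 8.6% and 7.2% for the 1-to-3-year contrast, and 5.2% when all correlations were equal.

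**Step 3: what is not affected.** The variance of a child's mean over three visits is proportional to (1 + 2m)/3, which depends on the correlations only through m. The random-intercept model gets that right, so the time-averaged group effect keeps a correct standard error.

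**Step 4: a second parameterisation.** Let q be slope variance divided by residual variance. With three equally spaced visits, the ratio for the group-by-time slope is √[(1 + q)/(1 + 2q)]: 1.00 at q = 0, 0.91 at q = 0.25, 0.82 at q = 1. In 20,000 simulated trials per setting, random intercept alone rejected 5.2%, 7.5% and 11.8%. An analysis allowing for both intercept and slope variation rejected 5.0% to 5.1%.

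**Reading the two sizes together.** The decay scenarios in step 2 have r13 of 0.2 to 0.3. The matching precision gain is therefore 53 to 56 per arm. The 68 per arm at r = 0.5 belongs to a different scenario and should not be added to the type I error figures.

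**The case against.** The strongest reply is that this is a condensed article, and that covariates, covariance structure and baseline handling usually sit in a statistical analysis plan. That stands as to anything left unsaid. It does not cover the methods that the article does name, which can be judged as written.

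Several stronger readings are tempting and are not supported:

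- A reader might infer that the plan discards the baseline altogether. Only the t-test does. The mixed model takes enrolment as one of its three time points.
- A reader might infer that standard errors will be too small. Random intercept alone is one option under consideration, not a commitment. Even then the error is limited to certain contrasts, needs unequal correlations or varying slopes, and reverses for the 2-to-3-year change.
- A reader might take the random-slope option to have no intercept. The phrase is ordinary shorthand for intercept plus slope, and that option largely removes the type I error problem.
- A reader might infer that age at test is not adjusted for. The section gives no covariate list for the mixed model and includes age, sex and date of birth in the data set, so silence proves nothing.

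It is also fair to say that nothing makes the t-test the primary analysis of Group A versus B. The section speaks of differences between and within the wasted and non-malnourished cohorts, and the sample size is framed on well-nourished versus wasted children. The point here is confined to the randomised comparison.

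**Conclusion.** The point holds in limited form. For Group A versus B, the named t-test is valid but leaves precision unused: 51 per arm could do the work of 53, 56 or 68 at assumed correlations of 0.2, 0.3 or 0.5. On the plan's own one-sided footing that lifts power by roughly 1 to 9 percentage points; at the lower correlations the gain is small.

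For the mixed model, the choice of random effects matters only if random intercept alone is adopted and correlation falls with time. In that case the 1-to-3-year group contrast has a standard error about 9-13% too small and type I error of about 7-9%. The correlations, equal variances and complete data are assumptions; the document supplies none of them. This is an improvement worth making in a stated method. It does not show that the randomised comparison is biased.

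**What to change.** For the randomised Group A versus B comparison, replace the t-test and the open random-effects choice with one mixed model of the 2- and 3-year scores. Include arm by visit, with baseline score, age at assessment and sex as covariates, and use an unstructured covariance between the two follow-up visits. Report the 3-year arm difference as the estimate.

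Confine this to the randomised arms. Baseline adjustment should not be presented as a causal correction in the comparisons with the well-nourished children, and the 3-year reference group has no earlier score to adjust for.

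The cost is wording and a few degrees of freedom. The variables are already scheduled for collection, so no visit or participant is added.
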